## 3. Discussion

This study presents an overview of a training program and a detailed description of the assessment methods in an older population with DM2. A properly prescribed and regularly performed physical activity is considered an essential tool for the management of DM2 and its complications [9]. However, low compliance rate to physical activity programs is one of the barriers faced by healthcare professionals, especially from the diabetic older population [60]. Therefore, new, effective, long-term and low-cost strategies to keep this population active are needed. WBV fits as a promising training modality that is feasible, practical and safe and, when combined with ST, can provide additional effects [61].

The assessment of vascular function is a primary outcome, aiming to reduce the risk of cardiovascular complications. The endothelium is essential to maintain vascular homeostasis; however, when dysfunctional, it loses its physiological properties and undergoes changes [18]. Thus, two important tools will be used, the infrared thermographic image (ITIV) and the portable vascular Doppler ultrasonography (UDV) for quantitative evaluation and mapping of these changes. ITIV is a useful method of assessment that allows the measurement and recording of the heat radiated by the skin surface, without providing ionizing radiation or physical contact [62], and UDV is a practical, relatively low-cost and sensitive method for assessing the mean blood flow in small vessels [63].

Functional mobility is also a primary outcome of this study, considering that important loss occurs during the aging process of people with DM2. Therefore, TUG is a simple and effective assessment method, for which high scores are associated with impaired balance, reduced gait speed and difficulty in activities of daily living [52].

Finally, if effective, this study will provide a nonpharmacological treatment option of innovative and scientific value.

## 4. Strengths and Limitations of the Study

The development of a protocol study for a single-blind, randomized, controlled clinical trial that is able to identify whether whole-body vibration (WBV) provides additional benefits to strength training (ST) in lower-limb blood flow and mobility in older adults with type 2 diabetes mellitus (DM2). The vibrating platform is safe equipment, easy to handle and low-cost, which minimizes the need for conscious effort; therefore, it is most suitable for obese and sedentary patients. This new tool may be a strategy for lower-limb blood flow assessment associated with infrared thermographic imaging analysis and mean peripheral arterial blood flow velocity evaluated by a handheld Doppler ultrasound to identify physiological changes. The limitations are an absence of clinical outcomes such as quality of life, and that the vibration sham (a device emitting a similar noise to WBV) can produce physiological effects due to static squatting.

## Figures and Tables

**Figure 1 diagnostics-12-01550-f001:**
[figure not shown]
Enrollment, randomization and assessment flow chart. DM2, type 2 diabetes; WBV, whole-body vibration; ST, strength training.

**Figure 2 diagnostics-12-01550-f002:**
[figure not shown]
Placement of markers in the body the volunteer according to the Davis protocol.

**Table 1 diagnostics-12-01550-t001:** Strength training regimens.

Set A	Set B
[figure not shown] Prone Plank Muscles Worked: Abdominal rectum, external oblique, serratus anterior, pectoralis major, tensor fascia lata, quadriceps.	[figure not shown] Prone Plank Muscles Worked: Abdominal rectum, external oblique, serratus anterior, pectoralis major, tensor fascia lata, quadriceps.
[figure not shown] Seated Low Row Muscles Worked: Trapezius, latissimus dorsi, rhomboids, posterior deltoid.	[figure not shown] Dumbbell Shoulder Press Muscles Worked: Anterior deltoid, lateral deltoid, triceps, trapezius, upper chest.
[figure not shown] Lat Pulldown Machines Muscles Worked: Latissimus dorsum, posterior deltoid, lower trapezius, rhomboids.	[figure not shown] Chest Fly Machine Muscles Worked: Pectoralis major, anterior deltoid.
[figure not shown] Upright Cable Row Muscles Worked: Lateral deltoid, trapezius, anterior deltoid, supraspinatus, infraspinatus, minor round.	[figure not shown] Triceps Pushdown Muscles Worked: Triceps, deltoid, forearm.
[figure not shown] Standing Bicep Curl (Cable) Muscles Worked: Biceps, brachialis, brachioradialis, anterior deltoid, forearm.	[figure not shown] Cable Hip Abduction Muscles Worked: Gluteus maximus, gluteus minimus, tensor fascia lata.
[figure not shown] Standing Leg Curl Muscles Worked: Isquiotibiales, gluteos, sural triceps.	[figure not shown] Cable Hip Adduction Muscles Worked: Long adductor, short adductor, magnum, gracilis, pectinous.
[figure not shown] Leg Extension Muscles Worked: Quadriceps, anterior tibialis.	[figure not shown] Standing Calf Raise Muscles Worked: Sural Triceps.

**Table 2 diagnostics-12-01550-t002:** Description of the whole-body vibration (WBV) protocol over 12 weeks.

Weeks	Time per Exercise (s)/Number of WBV Exercise	Frequency (Hz)	Rest Period (s)	WBV Total Time (s)
1–2	30/8	16	30	480
3–4	30/8	18	30	480
5–6	45/8	20	30	720
7–8	45/8	22	30	720
9–10	60/8	24	30	960
11–12	60/8	26	30	960

**Table 3 diagnostics-12-01550-t003:** Regions of interest (ROI) to be analyzed.

[figure not shown]	ROI: Anterior thigh region. Upper limit: groin. Lower limit: horizontal line aligned with the apex of the patella. Shape: ellipse, following the outline of the thigh.
[figure not shown]	ROI: Posterior thigh region. Upper limit: horizontal line aligned with the line gluteal. Lower limit: horizontal line aligned with the tip of the fibula. Shape: ellipse, following the outline of the thigh.
[figure not shown]	ROI: Anterior leg region. Upper limit: horizontal line aligned with the tip of the fibula. Lower limit: horizontal line above the malleolus. Shape: ellipse, following the outline of the lower leg.
[figure not shown]	ROI: Posterior leg region. Upper limit: horizontal line aligned with the tip of the fibula. Lower limit: horizontal line above the malleolus. Shape: ellipse, following the outline of the lower leg.
[figure not shown]	ROI: Dorsal foot region. Upper limit: horizontal line aligned with the talocrural joint. Lower limit: horizontal line aligned with the metatarsophalangeal joint. Shape: ellipse, following the outline of the foot.
[figure not shown]	ROI: Plantar foot region. Upper limit: horizontal line aligned with the heel tip. Lower limit: horizontal line aligned with the metatarsophalangeal joint. Shape: ellipse, following the outline of the foot.

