### 2.6. Intervention

The training protocol will last for 12 weeks (3 months) and comprise three times a week for 60 min each session. Before each session, the volunteers in arms G1 and G2 will be instructed by the intervention team to perform basic warming and stretching exercises accordingly to the Ramos protocol [21]. 

The ST consists of two sets (A and B) each to be performed alternately [39,40], as shown in Table 1, in accordance with recommendations of the American College of Sports Medicine (ACSM) for older adults [41] and Brazilian Diabetes Society (Sociedade Brasileira de Diabetes—SBD) [9]. A frequency of three days a week will be applied, very light to light intensity (40% to 50% of the test of a maximum repetition—1RM) and seven exercises involving the main muscle groups. In the 1RM test, a familiarization will be performed (pre-session), starting with 10% of body weight, progressing to the maximum lifting capacity, for a maximum of 5 attempts with an interval of 30 s between each attempt. The test will be performed bilaterally, starting with the nondominant side [42].

In addition, dumbbells and grounded muscle training equipment with different loads (Mega II, Marca Movement) will be used. The training will start initially with two sets of eight repetitions (1st to 4th week), progressing to two sets of twelve repetitions (5th to 8th week) and, finally, two sets of fifteen repetitions (9th to 12th week) [9,41]. The rest between sets will be sixty seconds and the load will gradually increase according to a good exercise performance. The strength training protocol will be applied to arms G1 and G2 equally.

Next, WBV will be applied through the Kikos P204–110v platform (Kikos Fitness, São Paulo-SP, Brasil), which has an oscillatory lateral vibration direction. The vibrating platform baseplate is slip-resistant for better safety during the training [7]. The amplitude (the vertical displacement of oscillatory motion) will be determined by the distance between both feet on the surface of the platform, ranging from approximately 2.0 mm to 5.0 mm [43]. A gradual increased in vibration frequency (the number of cycles of oscillation) and exposure duration was performed to avoid an early muscle activity decrease [44,45,46]. Vibration frequency and time spent between use and rest per week are described in Table 2.

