On the platform, barefoot volunteers will adopt an isometric squat positioning at 40°, verified with a conventional goniometer. On their heels, silicon insole will be applied (semi-rigid) in order to keep only the forefoot and middle-foot in direct contact with the platform surface, thus correcting the body weight distribution and foot biomechanics changes. Both strategies will be used to minimize the axial transmission to cranial base [7,21,47]. In accordance with the International Organization for Standardization (ISO) 2631-1, all the parameters are considered safe for body exposure to mechanical vibration [48].

The WBV sham (simulation) will be performed with the platform unplugged. A speaker connected to the platform will emit a similar sound during the time equivalent to the protocol, since the vibrating stimulus cannot be visually differentiated. The volunteers that experience the simulation will have to adopt the same squat positioning during the session. We will assure no contact between volunteers from arms G1 and G2 [47].

The volunteers in arm G3 group will be instructed to manage their diabetes as usual routine without practicing physical activity. All of them will be informed that they will be scheduled to receive the treatment after 12 weeks. 

It is worth mentioning that the entire intervention team will be submitted to a complete 8 h training. 

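### The columns of Table 2 do not agree with each other, so the vibration exposure and rest time per session cannot be fixed from the protocol

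*Protocol article*

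**What the plan says.** Section 2.6 (Intervention) describes a gradual rise in vibration frequency and exposure duration and leaves the timing to one table: "Vibration frequency and time spent between use and rest per week are described in Table 2". No other section gives a number of bouts, a rest period or a total vibration time.

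The columns of Table 2 are weeks, time per exercise and number of exercises, frequency (Hz), rest (s) and total WBV time (s). Its six rows form three pairs:

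- The first row is "1–2 30/8 16 30 480". The second, for weeks 3–4, differs from it only in frequency (18 Hz).
- The third row is "5–6 45/8 20 30 720". The fourth, for weeks 7–8, differs from it only in frequency (22 Hz).
- The fifth row is "9–10 60/8 24 30 960". The last, for weeks 11–12, differs from it only in frequency (26 Hz).

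Every row has 8 exercises and 30 s rest. The exercise time rises from 30 to 45 to 60 s and the total from 480 to 720 to 960 s. The table does not say whether the total includes rest.

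The sham in G2 takes its length from the same schedule: "A speaker connected to the platform will emit a similar sound during the time equivalent to the protocol". Section 2.6 also requires sham participants to hold the same squat.

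**The concern.** A total should follow from the number of exercises, the time per exercise and the rest. In weeks 1–4 it does, if rest is counted. From week 5 it does not, although the number of exercises and the rest are unchanged.

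Table 2 is the protocol's only definition of the experimental exposure. The hypothesis is that adding vibration to strength training brings further benefit, so the vibration dose is the quantity under test. If the columns cannot all be followed, the protocol does not say how long G1 participants vibrate and rest, a reader cannot reproduce the intervention, and the length of the G2 sham is left open in the same way.

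**Working it through.** **Inputs (Table 2).** n = 8 exercises and r = 30 s rest in every row; t = 30, 45 and 60 s per exercise in weeks 1–4, 5–8 and 9–12; stated total S = 480, 720 and 960 s. Sessions: 3 per week for 12 weeks = 36, so 12 in each four-week block.

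**Step 1: try to reproduce the stated totals from the printed columns.**

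| Reading | Formula | Weeks 1–4 | Weeks 5–8 | Weeks 9–12 |
|---|---|---|---|---|
| Stated | S | 480 | 720 | 960 |
| Elapsed, rest after each bout | n(t + r) | 8 × 60 = 480 | 8 × 75 = 600 | 8 × 90 = 720 |
| Elapsed, no rest after the last bout | nt + (n − 1)r | 240 + 210 = 450 | 360 + 210 = 570 | 480 + 210 = 690 |
| Vibration only | nt | 8 × 30 = 240 | 8 × 45 = 360 | 8 × 60 = 480 |

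The first elapsed-time formula reproduces weeks 1–4 only. The other two reproduce no row. None of these readings, each of which keeps 8 exercises and 30 s rest, gives 720 or 960 s.

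**Step 2: find what would reproduce them.** S/t = 480/30 = 720/45 = 960/60 = 16 in every row. Two departures from the printed columns give this:

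- *Rest equal to exercise time.* S/n − t = 60 − 30 = 30 s, 90 − 45 = 45 s and 120 − 60 = 60 s. This agrees with the printed 30 s in weeks 1–4 and contradicts it in weeks 5–12.
- *Sixteen bouts with rest not counted*, for example two rounds of 8. 16 × 30 = 480, 16 × 45 = 720, 16 × 60 = 960. This contradicts the printed 8 in all six rows. Weeks 1–4 would then agree with the elapsed-time formula only because exercise and rest happen to be equal there.

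**Step 3: size, if the total is elapsed time including rest.**

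- Weeks 5–8: 720 − 600 = 120 s per session (120/600 = 20%).
- Weeks 9–12: 960 − 720 = 240 s per session (240/720 = 33%).
- Over these 24 sessions: 12 × 120 + 12 × 240 = 1,440 + 2,880 = 4,320 s = 72 minutes.
- Over all 36 sessions: 12 × (480 + 720 + 960) = 25,920 s stated, against 12 × (480 + 600 + 720) = 21,600 s derived. The difference is again 4,320 s.

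**Step 4: size, if the total is vibration time.** Vibration per session is 480, 720 and 960 s instead of 240, 360 and 480 s, twice as much in every row. Over 36 sessions it is 25,920 s against 12 × (240 + 360 + 480) = 12,960 s.

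**Step 5: look for a tie-breaker.** Section 2.6 gives 60 minutes per session. Even 16 bouts of 60 s with 30 s rest take 16 × 90 = 1,440 s = 24 minutes, so session length alone does not exclude that reading. No section mentions two rounds or a rest period that changes over the weeks.

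**The case against.** The strongest reply is that exercise time, number of exercises, frequency and rest are printed for every row. Staff can run 8 bouts with 30 s rest and ignore the last column, which may simply be a wrong summary. If the total includes rest and the rest column is the faulty one, vibration stays at 240, 360 and 480 s per session and the extra 72 minutes are all rest. This stands as a possibility. But the document does not say which column is wrong, and the heading of the total column can be read as vibration time, in which case the exposure doubles. A fault confined to the last column is one explanation among several.

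A reader might infer three stronger things that the documents do not support:

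- *That the totals fit only with rest equal to exercise time, so that only weeks 5–12 are affected.* Sixteen bouts with rest uncounted fits equally well, and it puts weeks 1–4 in conflict too.
- *That participants receive 72 extra minutes of vibration.* The 72 minutes assume that the total includes rest, so they are a discrepancy in elapsed time.
- *That the G1–G2 comparison is confounded.* Section 2.6 has the sham follow the protocol time in the same squat, and the whole intervention team receives 8 h of training. If both arms use one reading, squat and rest times stay matched. Bias would need the arms to be run on different readings, and nothing in the protocol suggests that they would be. Section 4 concedes that static squatting in the sham can have physiological effects, so unequal timing would matter if it occurred.

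It is also true that neither the sample size (section 2.4) nor the analysis (section 2.9) uses these times.

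**Conclusion.** The inconsistency is real and lies in the printed figures: the rows are intact, progress regularly, and add up in weeks 1–4. With 8 exercises and 30 s rest, the totals for weeks 5–12 cannot be reached.

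The size depends on what the total means. Counting rest, it is 20% and then 33% above the derived time. Counting vibration only, it is twice the printed bouts in every row. Vibration per session is thus 360 or 720 s in weeks 5–8 and 480 or 960 s in weeks 9–12, and on the 16-bout reading weeks 1–4 are open too (240 or 480 s).

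The consequence is an unclear dose and an intervention that cannot be reproduced from the text, with the sham length inheriting the same doubt. The point does not establish bias between G1 and G2, and it leaves the power calculation and the planned tests untouched. It should be corrected, because Table 2 is the sole source of these times. The document alone cannot show which column is at fault.

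**What to change.** The sponsor should reconcile time per exercise, number of bouts, rest and total in all six rows of Table 2, including weeks 1–4. The table should state whether the total includes rest and, if there is more than one round, say so. Section 2.6 should then state that the reconciled bout and rest times, and the sound track, apply identically to the G2 sham. Which value is correct is for the clinical team to decide. If sessions have already been run, the report should give the timing actually used in each arm.

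The cost is one corrected table, a sentence in section 2.6 and a check with the intervention team. The sample size and the analysis do not change.

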## Data Availability

The results of our original study will be disseminated after completion in peer-reviewed journals and presented at conferences.
